**Exclusion criteria:**
1. Severe systemic illnesses (e.g., hepatic, renal, respiratory, cardiovascular, endocrine, hematological, oncological diseases)
2. Diagnosis of schizophrenia, bipolar disorder, dementia, substance dependence or abuse, or any primary psychotic disorder according to DSM-V criteria
3. Skin lesions or dermatological issues at electrode sites
4. Metal implants or electrically sensitive devices
5. Neurological conditions (e.g., stroke, seizure disorders) affecting cognition or treatment response
6. ECT within the past six months
7. Known hypersensitivity or contraindication to concurrent ECT medications
8. Pregnant or lactating
9. Receiving transcranial magnetic stimulation or other neuromodulation treatments
10. Participation in another concurrent clinical trial

### Randomization

Random sequences will be generated by a statistician with no other connection to the trial using Microsoft Office Excel 2017. The randomization sequence list will remain concealed from the investigators. Allocation concealment will be achieved through consecutively numbered, opaque, and sealed envelopes. A research nurse, uninvolved in any other study procedures, will assign the participants to their group to ensure objectivity and minimize bias.

### Blinding and unblinding

The tDCS treatment device consists of two parts: a computer and a small stimulator. To prevent participants from being directly aware of their group assignment, the treatment is carried out in a dedicated room, where the patient will sit on a couch positioned away from the computer and the stimulator will be placed in an opaque bag behind the patient. The psychiatrist administering tDCS knows the group assignments but cannot share this with participants or engage in the study’s evaluation or analysis. Additionally, the assessors and data analysts will be kept unaware of the intervention groups. To evaluate the adequacy of blinding procedures, participants will be invited to make an educated guess regarding their treatment assignment after the tDCS sessions.

If there is a suspicion of a severe adverse reaction or if clinical psychiatrists determine it is essential for participant safety, disclosure of group membership may be required.

### Intervention

tDCS will be administered using a battery-driven direct current stimulator (EM8010S, Yimai Medical Technology Co., Ltd. Wuhan, China) via a pair of identical squares (3 × 5 cm) saline-soaked sponge electrodes secured in place with elastic bands. The anodal electrodes will be positioned over the F3 site, corresponding to the DLPFC following the EEG10– 20 international system. Conversely, the cathodal electrode will be placed above the Fp2 site, corresponding to the right supraorbital region. Within two days after completing the ECT course, all study participants will receive tDCS five times per week, once daily, for two consecutive weeks. In the active tDCS condition, each session will deliver a direct current of 2 mA for 30 min. In the sham tDCS condition, stimulation will be administered using the same active tDCS montage. The stimulation intensity will be set at 2 mA, but the current will be applied for 1 min with a 30-s ramp-up and ramp-down. In prior studies [53], this approach ensured participant blinding regarding the stimulation type (active vs. sham).

During the intervention, participants will continue their usual pharmacotherapy, but transcranial magnetic stimulation or other neuromodulation treatments are forbidden. The intervention will be discontinued if there are any severe adverse effects or withdrawal. This trial is deemed of minimal risk to study participants. Therefore, there are no provisions for ancillary or posttrial care.

### ECT regimen

The ECT regimen, initially up to four times in the first week and then adjusted to three times weekly, is determined by the treating psychiatrist. It will be conducted using a Thymatron DGx apparatus, with bitemporal electrode placement 5 cm above the outer angle of the orbit. The initial electric charge is calculated using the half-age method, with subsequent dosages adjusted based on EEG seizure activity, increasing by 5% each session. The ECT uses square-wave stimulation at 900 mA, with 125 bidirectional pulses per second and a brief-pulse width of 1.5 ms. Anesthesia involves intravenous atropine (0.5 mg), propofol (2 mg/kg), and succinylcholine (1 mg/kg). Subsequent dosages will be adjusted according to the patient's response to achieve appropriate seizure morphology. We will assess seizure adequacy based on morphology and duration, including polyspike wave, 3-Hz spike and wave activity, and postictal suppression [54]. ECT effectiveness will be defined by induced electroencephalograph seizure durations exceeding 25 s [55].

### Outcome

To assess cognitive changes, we will employ the CANTAB, a tool previously demonstrated to be highly sensitive in evaluating the cognitive side effects of ECT [5, 6]. Additionally, we have chosen a set of five tests designed to assess frontal lobe function. To mitigate potential learning effects, different parallel versions of the same test will be employed during various assessment phases. Assessments of cognitive function and depressive symptoms will be conducted before the first tDCS session (T0), immediately after the last tDCS session (T1), 2 weeks post-tDCS (T2), and 4 weeks post-tDCS (T3). The detailed visit procedure is shown in Table 2.

**Table 2 Tab2:** Schedule of enrolment, intervention, and assessments

	Enrolment	Baseline	Intervention	Follow-up	
		Before tDCS	After tDCS	after 2 weeks	After 4 weeks
Time point		T0	T1	T2	T3
Enrolment					
Eligibility screening	√				
Informed consent	√				
Allocation	√				
Demographic data		√			
Intervention					
Active tDCS			√		
Sham tDCS			√		
Assessments					
CANTAB					
SRM		√	√	√	√
SWM		√	√	√	√
RVP		√	√	√	√
VRM		√	√	√	√
SOC		√	√	√	√
HAMD-24		√	√	√	√
SDS		√	√	√	√
tDCS-AEQ^a^			√		
Blinding			√		

*a: test after every tDCS session*

*CANTAB: Cambridge Neuropsychological Test Automated Battery, HAMD-24: Hamilton depression rating scale; RVP: Rapid visual information processing; SDS: Self-rating depression scale; SOC: Stockings of Cambridge; SRM: Spatial recognition memory; SWM: Spatial working memory; VRM: Verbal Recognition Memory; tDCS, transcranial direct current stimulation; tDCS-AEQ: Transcranial direct current stimulation adverse effects questionnaire*

### Primary outcome

The primary outcome measured is the change in Spatial Recognition Memory (SRM), which assesses spatial recognition memory using a forced-choice paradigm. In the first phase, participants are presented with a series of 5 white boxes, each at a different spatial location on the screen. During this phase, participants are instructed to remember the locations of these white boxes. In the second phase, two boxes are simultaneously presented. The target box occupies a location from the first phase, while the distractor box is placed in a previously unused location. Participants must recognize and click on the target box. This process is repeated four times, with new target and distractor locations in each test. The percentage of correct responses will be recorded as part of this assessment.

### Second outcome

Spatial Working Memory (SWM) assesses the subject's ability to retain and manipulate spatial information in working memory. The outcome measures include between errors, within errors, and strategy employed. A high strategy score represents poor use of strategy, and a low score equates to effective use.Verbal Recognition Memory (VRM) evaluates immediate and delayed verbal information memory. Outcome measures include the total number of correct words in the free recall phase, the total of all correctly identified words in the immediate recognition phase, and the delayed recognition phase.Rapid Visual Information Processing (RVP) assesses visual sustained attention. Outcome measures include mean latency and total correct responses.Stockings of Cambridge (SOC) evaluates spatial planning and spatial working memory. Outcome measures include the number of n-move problems solved in the minimum moves, mean moves for n-move problems, mean initial thinking time for n-move problems, and mean subsequent thinking time for n-move problems.Assessing the degree of depressive symptom with the Hamilton Depression Rating Scale (HAMD-24) [56] and the Self-rated Depression Scale (SDS) [57, 58].

### Harms

All participants will complete the tDCS adverse effects questionnaire (tDCS-AEQ) after each tDCS session to evaluate potential adverse effects of the intervention. Common adverse reactions, as indicated by a systematic review [59], include tingling sensations, itching, mild skin redness, and discomfort in the stimulation area. Participants will rate their experienced adverse events on a 0 to 5 scale. Serious adverse events (SAEs) or reactions are considered unlikely based on the review. Only unexpected serious adverse events or reactions unrelated to these clinical procedures will be reported as SAEs.

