**Discussion:**

We describe a novel clinical trial to explore whether the administration of tDCS after completing ECT course can accelerates recovery from the CSEs. We hypothesized that the active group would recover faster from the CSEs and be superior to the sham group. If our hypothesis is supported, the use of tDCS could benefit eligible patients who are reluctant to receive ECT and reduce the risk of self-inflicted or suicide due to delays in treatment.

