### Study design and setting

This is a randomized, double-blind, sham-controlled, interventional trial. 60 eligible participants will be recruited within two days after the last ECT session and randomly allocated into two groups in a 1:1 ratio: active tDCS (intervention group) and sham tDCS (control group). Assessments will be conducted at the following time points: before the first tDCS session (T0), immediately after the last tDCS session (T1), 2 weeks post-tDCS (T2), and 4 weeks post-tDCS (T3), using the Cambridge Neuropsychological Test Automated Battery (CANTAB). Table 2 shows schedule of enrolment, intervention, and assessments. Throughout the study, there was no interference or restriction for the patient ‘s physician in charge to adjust psychiatric medications according to the patient’ s condition. Figure 1 represents the research procedure schematically.

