## Discussion

This is the first RCT aimed at using tDCS to assist in the recovery of CSEs caused by ECT in depression patients. Given that CSEs might hinder patients from opting for ECT [60], identifying a rehabilitation strategy could assist patients in alleviating these concerns.

Depressive patients exhibit an imbalance in cortical metabolism between the two hemispheres, with lower metabolism observed in the left frontal lobe compared to the right frontal lobe [61, 62]. ECT can induce a short-term reduction of CBF and metabolism in frontal lobe, but this alteration subsequently normalizes within around one month [13].

By utilizing the anode at left DLPFC and the cathode at right DLPFC, tDCS aims to rectify the cortical imbalance in depression, ultimately ameliorating depressive symptoms [61]. Although the mechanisms underlying the impact of tDCS on cognitive function remain not entirely clear, early research suggests that tDCS may elicit long-term effects extending beyond the stimulation period [49, 63, 64]. Otherwise, these enduring effects are likely mediated through the modulation of N-methyl-D-aspartate and gamma-aminobutyric acid receptor activity [65, 66].

Cognitively, depression in the elderly is intricately linked with dementia; past studies have suggested that depressive symptoms might be a precursor to dementia [67, 68]. Despite improvements in depressive symptoms, elderly patients often continue to exhibit deficits in visuospatial ability, information-processing speed, and delayed memory [69]. This complexity adds to the challenge of distinguishing whether cognitive deficits in elderly patients post-ECT are due to ECT itself or pre-existing conditions. Further research indicates that while ECT treatment may lead to short-term cognitive decline in elderly patients [70], there is potential for long-term cognitive improvement [71]. Therefore, enhancing cognitive function during symptom remission in elderly patients with depression is of critical clinical importance, a goal that requires further dedicated efforts [72].

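### Scheduled adverse-event enquiry stops with the last tDCS session, so about two thirds of the time on study (T1 to T3) has none

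*Protocol article*

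**What the plan says.** The Harms section of the protocol article gives the collection rule: "All participants will complete the tDCS adverse effects questionnaire (tDCS-AEQ) after each tDCS session to evaluate potential adverse effects of the intervention". Participants rate what they experienced from 0 to 5, and the reactions named as common are local ones such as tingling, itching, redness and discomfort where the current is applied.

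Table 2, in the Outcome section, sets the same schedule. The questionnaire row carries one tick, in the T1 column, with the footnote "test after every tDCS session". The row is empty at T2 and T3. At those two visits the table schedules the five CANTAB tests, HAMD-24 and SDS, which the article defines as the primary and secondary outcomes.

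The Harms section also has a sentence on which serious adverse events are reported. It gives no start or end date for that reporting and no visit at which participants are asked about such events.

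The Intervention section fixes the length of treatment: "all study participants will receive tDCS five times per week, once daily, for two consecutive weeks". Study design and setting places T2 two weeks and T3 four weeks after the last session.

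**The concern.** A questionnaire completed at the end of a stimulation session cannot record an event that happens after the last session. Since it is the only scheduled harms instrument, nobody is due to ask about adverse events between T1 and T3, although participants attend twice in that period.

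This matters because many participants will be at home by then. The Recruitment section has leaflets handed out shortly before discharge, and the limitations in the Discussion refer to discharged patients travelling to the hospital. A self-harm act, an admission elsewhere or a new physical symptom need not come to the notice of study staff. If such events are recorded only when volunteered, the counts by arm are incomplete to an unknown degree.

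The trial does draw conclusions over the follow-up. The Objective section makes cognition after four weeks, and relapse of depressive symptoms, secondary aims. A report that gives benefit to T3 would naturally carry a safety statement for the same period, and the planned harms data would not support one.

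**Working it through.** The article gives no figure for harms coverage, so there is none to reproduce. The check sets the schedule out by period and then computes the share of time without scheduled enquiry.

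**Schedule by period (Harms; Table 2)**

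| Period | Scheduled adverse-event enquiry | Other scheduled assessments |
|---|---|---|
| First session to T1 | tDCS-AEQ after every session: 5 × 2 = 10 sessions | CANTAB, HAMD-24, SDS at T0 and T1 |
| T1 to T2 (2 weeks) | none | CANTAB, HAMD-24, SDS at T2 |
| T2 to T3 (2 weeks) | none | CANTAB, HAMD-24, SDS at T3 |

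**Share of time after T1**

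Inputs:
- Follow-up F = 4 weeks = 28 days (Study design and setting).
- Treatment length D = two weeks of five sessions (Intervention). The article does not say on which weekday treatment starts, so D is 14 days nominally, 12 calendar days for ten sessions from a Monday to the second Friday, or 11 days elapsed between the first and last of those sessions.
- Lead-in G = 0 to 2 days, from "60 eligible participants will be recruited within two days after the last ECT session". It counts only if time on study is taken to start at the last ECT session.

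Formula: share = F / (G + D + F).

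| Counting rule | Calculation | Share |
|---|---|---|
| Nominal 2 + 4 weeks | 28 / (0 + 14 + 28) = 28/42 | 66.7% |
| 12 calendar days of treatment | 28 / (0 + 12 + 28) = 28/40 | 70.0% |
| 11 elapsed days of treatment | 28 / (0 + 11 + 28) = 28/39 | 71.8% |
| 11 days plus 2-day lead-in | 28 / (2 + 11 + 28) = 28/41 | 68.3% |
| 14 days plus 2-day lead-in | 28 / (2 + 14 + 28) = 28/44 | 63.6% |

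The range is 64% to 72%. The nominal figure of two thirds is the safest to quote, and the conclusion does not depend on the choice.

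**What would still be seen after T1**

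- Mood: HAMD-24, rated by a psychiatrist blinded to allocation (section on data collection and management), and SDS.
- Cognition: all five CANTAB tests.
- Both are compared between arms, because the Statistical methods section applies mixed models for group and time effects to primary and secondary outcomes.
- Not covered: self-harm acts, hospital admissions, and events that are neither mood nor cognition. These depend on unsolicited reporting.

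**The case against.** The strongest reply is that T2 and T3 do carry information on harm. A reader might infer from the empty questionnaire row that psychiatric harm after T1 could not be seen at all, or that the trial follows benefit for six weeks and harm for only two. The documents do not support that. HAMD-24, SDS and CANTAB are measured at both visits and modelled by arm, and relapse is a stated aim. Listing them as outcomes does not stop them showing deterioration. This part of the objection stands and narrows the point to acts, admissions and other events that those scales do not record.

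A reader might also cite two other statements in the article, and neither helps. The abstract says that the treatment could "reduce the risk of self-inflicted or suicide due to delays in treatment". That concerns patients who are reluctant to have ECT, whereas trial participants have completed it, so it says nothing about their risk after tDCS. The Discussion says that "tDCS may elicit long-term effects extending beyond the stimulation period". That sentence is about mechanisms of the cognitive effect. It is not given as the reason for T2 and T3, and it does not speak of delayed harm.

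A third reply is that an article condenses, and that open adverse-event questions and reporting windows usually sit in the full protocol. This is fair for the reporting of serious events, where the article sets no end date; an event volunteered after T1 could still be reported. It does not answer the schedule itself, which the Harms section and the visit table both state and on which they agree.

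Finally, the share is one of calendar time and not of risk. The reactions the article expects are local and tied to stimulation, so the questionnaire is placed where most of them should occur. That is right, and it is why the percentage should not be read as a percentage of events missed.

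**Conclusion.** The point holds in limited form. The schedule as stated leaves the four weeks from T1 to T3 without any scheduled adverse-event enquiry, which is 28 of 42 nominal days for each participant who completes follow-up. Worsening mood and cognition would still be visible by arm. Self-harm acts, admissions and other new physical or late events would be known only if volunteered, so a safety statement covering the follow-up would lack support.

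This rests on reading Table 2 as the complete list of scheduled assessments, and on no further adverse-event enquiry being laid down in a fuller protocol that is not shown. The primary analysis is unaffected. It is an inexpensive gap that is worth closing, and it is best closed before participants reach T2 and T3, because later recall would not fully replace asking at the visit.

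**What to change.** In Table 2, add an adverse-event row ticked at T2 and T3, and also at T1 to pick up events between sessions. Use one short standard question or self-completed form covering new or worsened symptoms, self-harm and hospital admission since the last visit. Record the answers in the CRF and tabulate them by arm. Add a sentence to the Harms section stating that harms collection runs from the first tDCS session to T3.

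The cost is one CRF page and a few minutes at visits that already take place. No extra visit or separate member of staff is needed: a fixed question or self-completed form does not call for the psychiatrist who gives tDCS and knows the allocation. Treatment, eligibility, endpoints and sample size are unchanged.

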### Date collection methods and management

CANTAB is a computer-administered battery of tasks, and the primary outcome variables from the CANTAB tasks will be automatically calculated by the software. A clinical senior psychiatrist blinded to the group allocation will assess the severity of depressive symptoms using HAMD-24.

All participant demographic and scale related results will be recorded in the case report form (CRF). For patient privacy, irrelevant personal information like names, contact numbers, and addresses will be omitted during data entry, using patient numbers for identification. The original CRFs are securely stored and accessible only to the project leader and principal investigator.

Our trial does not have a data monitoring committee, but the subject group has a dedicated person to oversee. We will notify patients to come for tDCS via WeChat (a popular social communication app in China) and reimburse their transportation costs to improve patient compliance.

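### As written, the SAE rule drops serious events for being expected and, on its most natural reading, for being related to the procedures

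*Protocol article*

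**What the plan says.** The Harms section describes two things. The first is a questionnaire: "All participants will complete the tDCS adverse effects questionnaire (tDCS-AEQ) after each tDCS session to evaluate potential adverse effects of the intervention". Symptoms are rated from 0 to 5, and the common reactions listed are tingling, itching, mild skin redness and local discomfort. The second is serious events. The text states that "Serious adverse events (SAEs) or reactions are considered unlikely based on the review" and then sets the rule: "Only unexpected serious adverse events or reactions unrelated to these clinical procedures will be reported as SAEs".

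Three other places bear on serious harm:

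- **Blinding and unblinding:** group membership may be disclosed on safety grounds, including "If there is a suspicion of a severe adverse reaction".
- **Intervention:** "The intervention will be discontinued if there are any severe adverse effects or withdrawal".
- **Date collection methods and management:** "Our trial does not have a data monitoring committee", though a dedicated person is to oversee the trial. The limitations paragraph of the Discussion adds that there is no independent steering or monitoring committee and that a management group of study researchers oversees daily operations.

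**The concern.** Seriousness, expectedness and relatedness are three separate judgements. Seriousness decides whether an event is an SAE; the other two describe it. The Harms sentence uses the describing attributes to decide whether a serious event is reported at all. On its natural reading it also filters in the wrong direction, because the events it removes are those that the treatment caused.

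This is more than a detail left to a fuller document. The article states a rule and makes it exclusive with its first word.

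What is at stake is the harms conclusion. A sham-controlled trial should let the reader compare serious events between arms. If related events are removed before counting, the trial could keep to its own rule and report no SAEs although serious reactions to stimulation had occurred.

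**Working it through.** The protocol states no figure on this point, so there is none to reproduce. The check is to apply the sentence to each class of serious event under each reading that its grammar allows, and then to look for another section that supplies what is lost.

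**Step 1. The readings.** The sentence is open in two ways. The word *unrelated* may limit both nouns (events and reactions) or only *reactions*. The phrase about clinical procedures has no clear antecedent; tDCS is the only procedure that the Harms section names, but ECT could be meant.

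- A: both filters apply to all serious events, and the procedure is tDCS. This is the most natural reading.
- B: *unexpected* limits the serious events and *unrelated* limits only the reactions; the procedure is tDCS.
- C: both filters apply, but the procedure is ECT only.

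**Step 2. What is reported as an SAE.**

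| Class of serious event | A | B | C |
|---|---|---|---|
| Unexpected, not caused by tDCS | yes | yes | yes, unless caused by ECT |
| Unexpected, caused by tDCS | no | yes | yes |
| Expected, not caused by tDCS | no | only if it counts as a reaction | no |
| Expected, caused by tDCS | no | no | no |

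Reading A loses three of the four classes. Readings B and C rescue unexpected events caused by tDCS but still lose expected ones. If B and C are combined, an expected serious reaction to tDCS could be kept as a reaction unrelated to ECT. Expected serious events that are caused by ECT, or that do not count as reactions, would still be lost. No reading gives a complete count.

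**Step 3. Does another section supply what is lost?**

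- The tDCS-AEQ is a self-rating after each session. Table 2 marks it only in the T1 column, so it does not cover the four weeks of follow-up to T3, and it is not described as a route for SAEs.
- Blinding and unblinding and Intervention say what happens to the blind and to the treatment after a severe reaction. Neither says that the event is reported as an SAE. They also use *severe*, which is not the same term as *serious*.
- The overseer and the management group are not described as reporting serious events by arm.

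**Step 4. Direction of the bias.** Intervention gives 5 sessions a week for 2 weeks, so 5 × 2 = 10 sessions. Active stimulation lasts 30 × 10 = 300 minutes in total. Sham current lasts 1 × 10 = 10 minutes, or 2 × 10 = 20 minutes if the two 30-second ramps come on top. Serious events caused by stimulation would therefore be expected mainly in the active arm. A filter that removes related events would remove more from that arm and would pull the comparison towards no difference.

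**The case against.** The strongest reply is that the sentence is a drafting slip in a condensed article, perhaps with *unrelated* written for *related*, and that its grammar permits milder readings. The ambiguity is real. A reader might infer that every related serious event is certain to go unreported, but the document does not support that as a certainty: under B or C an unexpected serious event caused by tDCS would be reported. The possibility of a slip does not save the text, because a slip is still a rule stated wrongly.

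A reader might also infer that particular psychiatric events, foreseeable in recently treated depression, would be filtered out as expected. The document does not say so. The only reactions it lists are mild local ones, and no serious event is designated as expected. What the *unexpected* filter removes in practice therefore depends on a designation that the article does not give.

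A third tempting inference is that the SAE listing is the only formal way in which serious harm could come to light. That goes too far. The session questionnaire, the discontinuation and unblinding provisions, the overseer, the management group, and the HAMD-24 and SDS at T0 to T3 could all bring a problem to notice. What stands is narrower: none of them is described as reporting serious events by arm.

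Finally, one might attach an upper confidence limit for a zero count in 30 active patients. That limit would be the same under a correct rule, so it does not measure this defect.

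It is also fair to say that safety is not among the stated objectives, and that the primary outcome, sample size and efficacy analysis are untouched.

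**Conclusion.** The point holds: the SAE sentence is wrong as written and nothing else in the document corrects it. On the most natural reading it excludes every serious event related to the procedures and every expected one. With either alternative taken singly, some expected serious events are still lost, including those related to tDCS; even with both combined, some expected serious events are lost.

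The size can be stated only as classes of event: three of four on the natural reading, fewer on the others. The bias towards no harm rests on two assumptions: that serious events caused by stimulation would occur at all, which the protocol considers unlikely but not impossible, and that they would follow exposure and so fall mainly in the active arm. The conclusion concerns the validity of the safety statement. It does not show that any serious event would go unnoticed by the study team.

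**What to change.** Replace the sentence in Harms with wording such as: *All serious adverse events from allocation to T3 will be recorded and reported by arm, regardless of expectedness or relationship to tDCS or ECT; expectedness and relationship will be recorded as classifications.* Starting at allocation covers the interval before the first session, since Table 2 places allocation at enrolment. Naming both tDCS and ECT removes the doubt about which procedures are meant.

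The new sentence must then be reconciled with the severe-reaction wording in Blinding and unblinding and in Intervention, so that it is clear how *severe* and *serious* relate and that events handled there also enter the SAE record. This changes only recording and reporting; the discontinuation rule itself is left to the investigators.

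The cost is one protocol sentence, matching guidance for the case report form, and slightly more reporting. No sample size, power or efficacy analysis changes.
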